#### Recruitment, randomization, and blinding

Participants are recruited from outpatient settings in Hamburg (i.e., clinical psychologists and psychiatrists in private practice, social services), psychiatric clinics, and local self-help groups. Participants are either referred to the study by practitioners or via self-referral.

Enrolled and potentially eligible participants are invited for a study information meeting with a trial therapist. The participant will receive a copy of the participant information sheet which provides detailed information about the aims of the study and trial procedures. Participants are given the opportunity to ask questions. Following the information meeting, participants have sufficient time (24 h to 1 week) to consider their participation. After providing informed consent, participants meet with a trial rater who assesses eligibility and completes the baseline assessment with eligible participants. Clinical interviews are conducted by trial raters (psychologists in clinical training with at least master’s degree). All raters have already undergone training in basic therapeutic skills, such as assessment and building rapport. All raters receive a 4-h rater training by the trial manager on all of the observer-rated measures used in this trial. Allocation to either treatment- or wait-list control group is conducted (1:1) using permuted blocks of 4, 6, and 10 to reduce predictability of the sequence. The randomization schedule is generated and preserved by an assistant of the work group who is not otherwise involved in trial procedures. The trial manager is informed about the participant’s group allocation and notifies the participant and the responsible trial therapist.

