#### Sample size

An a priori power calculation is not appropriate for this feasibility trial as the study aim is not to test efficacy. Nonetheless, we aim to examine first effect size estimates of “Goals in Focus” on our primary and secondary outcomes. These estimates will inform the sample size calculation for a future fully powered RCT. Based on the recommendations for feasibility studies [75] and on existing feasibility trials in this field [76, 77], the target for this feasibility study was set at *N* = 30 participants (*n* = 15 intervention group; *n* = 15 wait-list control group).

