#### Analysis plan

Feasibility and acceptability will be analyzed by calculating descriptive statistics based on the intention-to-treat (ITT) population. Potential reasons for trial withdrawal will be examined by comparing baseline characteristics (e.g., symptom severity, sociodemographic variables, etc.) between participants who completed the trial and participants who discontinued their participation after randomization.

Clinical outcomes at baseline assessment (*t*_0_) and 6-month assessment (*t*_1_) will be summarized using descriptive statistics (i.e., frequency and percentages on binary and categorical variables; means, standard deviations, or medians, with minimum and maximum values for continuous variables) for each arm of the trial separately. Wait-list control and treatment group characteristics at baseline will be compared using Pearson chi-square tests for the categorical variables and the *t*-test or Mann–Whitney test for the quantitative variables.

Confirmatory analysis will be conducted for primary and secondary outcomes based on the ITT population. An ANCOVA adjusted for baseline values will be calculated with group allocation as between-subject factor and time as within-subject factor. Any variables that show significant group differences at baseline or are found to correlate with the primary outcome (e.g., age, gender, diagnosis, medication doses, duration of illness, symptom severity, etc.) will be entered as covariates. Effect sizes between and within treatment conditions will be assessed by calculating Cohen’s *d*. Missing values will be handled by multiple imputation, if missing completely at random [93]. All analyses will be carried out using validated statistical software.

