“Goals in Focus” was developed to directly target the relevant motivational negative symptom domains by translating recent empirical research on factors and mechanisms underlying motivational negative symptoms into specified interventions. The comprehensive treatment approach is tested in a randomized controlled trial design which allows to eliminate a possible selection bias and to control for spontaneous remission effects. However, there are some limitations to our study design: this is a pilot trial with the main focus on feasibility and the sample of 30 participants is not sufficient for a reliable efficacy analysis. As likelihood of type 1 error inflation is high, results of significance tests cannot be interpreted, but effect sizes derived from the present study will be used for a priori sample size calculation for a subsequent fully powered RCT. The advantage of a wait-list control condition is that it allows a first estimation of effects and enables wait-list participants to later receive the same intervention. Also, diffusion effects between the conditions (e.g., patients from the wait-list group receiving information about the intervention from other patients, therapists including intervention elements in standard treatment) are unlikely due to the outpatient setting and the fact that treatment as usual is not provided by trial therapists. A disadvantage is that the wait-list comparator may artificially inflate estimates of the intervention effect, due to participants being held in a waiting position and less likely to initiate behavioral change on their own (e.g., as suggested by Cunningham et al. [94]). Additionally, the eligibility criterium of “being able to engage in weekly therapy sessions of 50 min” limits the generalization of effects to those who are not able to attend weekly sessions for the full-time range of 50 min. Other issues that warrant mention relate to the selected outcomes: since “Goals in Focus” aims at improving goal setting and achievement, the EMA of goal pursuit is of particular interest. However, participants’ adherence to an autonomously conducted 1-week survey might be reduced, which is why we did not select it as the primary outcome. Also, a long-term follow-up was not included at this point due to the primary focus being on acceptability, feasibility, and first estimates of efficacy. It also needs to be kept in mind, that the intervention only targets motivational negative symptoms and not expressive negative symptoms, the other relevant component of negative symptoms [72, 95]. However, we expect expressive negative symptoms to be indirectly affected by the intervention as suggested by results reported by Choi et al. [18] in relation to a similar treatment approach. Accordingly, expressive negative symptoms are evaluated as a secondary outcome. Similarly, the intervention does not target contextual factors, such as social deprivation or health-related issues that are likely to exacerbate negative symptoms, but expect the achievement of personal goals due to the intervention to partially improve participants’ challenging contextual factors as well.

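### Multiple imputation is tied to data missing completely at random, the wrong condition, and no method is named for the missing-at-random case

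*Protocol article*

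**What the plan says.** All the relevant text on method is in the Analysis plan section of the protocol article. The only rule for missing clinical outcome data is "Missing values will be handled by multiple imputation, if missing completely at random", with a literature citation. No other section qualifies it, and no method is given for data that are not MCAR.

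The same section commits to a population: "Confirmatory analysis will be conducted for primary and secondary outcomes based on the ITT population". The model is "An ANCOVA adjusted for baseline values will be calculated with group allocation as between-subject factor and time as within-subject factor". Variables that differ between groups at baseline or correlate with the primary outcome are to be added as covariates. The effect measure follows: "Effect sizes between and within treatment conditions will be assessed by calculating Cohen"'s *d*. The section also plans to look into dropout: "Potential reasons for trial withdrawal will be examined by comparing baseline characteristics" between those who complete the trial and those who stop after randomisation.

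The Sample size section sets 15 per arm and states "An a priori power calculation is not appropriate for this feasibility trial as the study aim is not to test efficacy". The Discussion says that significance tests cannot be interpreted, but that "effect sizes derived from the present study will be used for a priori sample size calculation for a subsequent fully powered RCT".

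**The concern.** The three standard missing-data mechanisms call for different handling. Under MCAR, those observed are a random subset of those randomised, so complete cases give an unbiased effect and imputation adds at most some precision. Under MAR, missingness depends on recorded variables, and imputation that uses those variables can remove bias. If missingness depends on the unseen outcome itself (MNAR), imputation helps only in part. The article attaches imputation to the first mechanism, where there is no bias to remove, and names nothing for the second.

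The condition also cannot be applied reliably. MCAR cannot be proved from data, and a sample of 30 can hardly detect departures from it.

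At stake is the effect size. Participants are selected for motivational negative symptoms, and one arm attends up to 24 weekly sessions while the other waits, so dropout could plausibly be related to patient characteristics and could differ by arm. The planned comparison of completers with discontinuers shows that the authors allow for this. The effect size is what the trial passes on to the sizing of the next one.

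**Working it through.** The article states no figure tied to this rule: no dropout rate, no power and no assumed effect. There is nothing to reproduce, so the check is of the logic. Only the 15 per arm comes from the article; all other inputs below are assumptions.

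**1. Can MCAR be checked with 30 participants?** Take a two-sample *t* test of dropouts against completers on one baseline variable, two-sided 5%, 28 degrees of freedom, noncentrality = δ × √(n₁n₂/(n₁+n₂)).

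| Dropouts vs completers | √(n₁n₂/(n₁+n₂)) | Power at δ = 0.5 SD | Power at δ = 0.8 SD |
|---|---|---|---|
| 6 vs 24 | √(144/30) = 2.19 | 0.185 | 0.395 |
| 3 vs 27 | √(81/30) = 1.64 | 0.125 | 0.246 |

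A non-significant result would say very little about MCAR.

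**2. Where does complete-case analysis go wrong, and does imputation help?** Simulation of 4,000 trials per mechanism with 15 per arm, SD 1, baseline-to-6-month correlation 0.5, true benefit 0.5 SD, overall dropout 19% to 24%, and one recorded auxiliary variable related to outcome. There were 10 imputations from one model with arm, baseline and the auxiliary. Except under MCAR, dropout depended on the named variable in the intervention arm only. Entries are bias in SD units; negative means that benefit is overstated.

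| Mechanism | ANCOVA, complete cases | ANCOVA, imputed | Unadjusted difference, complete cases | Unadjusted difference, imputed |
|---|---|---|---|---|
| MCAR | −0.01 | −0.01 | −0.01 | −0.01 |
| MAR, via baseline score | −0.01 | −0.01 | −0.15 | −0.01 |
| MAR, via recorded auxiliary | −0.17 | −0.01 | −0.17 | −0.02 |
| MNAR | −0.15 | −0.10 | −0.20 | −0.10 |

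- Under MCAR, imputation changes only precision: the empirical SD of the ANCOVA effect is 0.355 imputed and 0.365 for complete cases, about 3%.
- If dropout depends on arm and baseline score, the adjusted effect is unbiased with or without imputation, because both are in the model. The unadjusted difference that underlies a raw between-arm *d* is not protected.
- If dropout depends on a recorded variable outside the model, the adjusted effect is biased too, and imputation with that variable removes nearly all of it.
- Within-arm *d* was not simulated. It is not baseline-adjusted either, so by the same reasoning it depends on who is left.

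**3. What could carry forward?** With two-sided 5% and 80% power (assumed), n per arm = 2 × ((1.96 + 0.8416)/d)². At d = 0.5 this is 62.8, so 63. If the auxiliary-driven bias turned 0.5 into 0.67, it is 35.0, so 35. For scale, the standard error of d with 15 per arm is about √(2/15) = 0.37, so a 0.17 SD bias is 0.17/0.37 ≈ 0.46 of one standard error.

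**The case against.** The strongest reply is that the consequence is inferred. The sentence says if, not only if. It names no MCAR test, no fallback and no complete-case analysis, and an article may leave a fallback to the full protocol or analysis plan. A reader might infer that evidence against MCAR switches imputation off and turns the promised analysis into a completer analysis. The document does not say that. The comparison of completers with discontinuers is there to explore reasons for withdrawal, not to decide whether to impute. If MCAR were judged by such a low-powered comparison, imputation would usually go ahead. This part of the objection stands. It does not rescue the condition itself, which is stated and is wrong as stated.

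A second reply is that differential dropout need not bias the result. This also stands in part. Arm and baseline score are in the ANCOVA, and further prognostic covariates may be added, which narrows the gap. What remains exposed is unadjusted or within-arm *d*, and the ANCOVA effect when dropout follows recorded variables outside the model.

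Third, any quoted size is hypothetical. One can assume 20% loss with the lost intervention participants 0.5 SD worse, which gives 0.2 × 0.5 = 0.10 SD, reads a true 0.4 as 0.5 and plans about 63 instead of 98 per arm. That would not measure this defect. The unseen outcomes are assumed, and if recorded variables do not predict them the mechanism is MNAR, where imputation recovers only part of the bias. Sampling error in d is larger than any of these biases.

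Fourth, a large imputation model could do harm, and this stands. At 20% loss about 12 participants per arm are observed. In simulations with separate models per arm and four to six uninformative predictors, the SD of the effect rose to about 0.42 to 0.46, against about 0.37 for complete cases. With arm and baseline only, it stayed at 0.37.

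**Conclusion.** The condition is misstated and should be corrected. Tying imputation to MCAR allows it where complete cases are already unbiased, rests on something that 30 participants cannot verify, and leaves the missing-at-random case without a named method in an analysis declared to be intention-to-treat.

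The possible bias is confined to unadjusted or within-arm Cohen's *d*, and to the ANCOVA effect if dropout depends on recorded variables outside the model. The 0.15 to 0.17 SD found under MAR is illustrative: it rests on assumed dropout of 23% to 24%, an assumed correlation and an assumed auxiliary variable.

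The document does not support saying that the trial will report a completer effect size, or that the next trial will be undersized by a given number. Severity is should-fix: the feasibility outcomes are descriptive and do not depend on this rule, and the article itself says that the significance tests are not to be interpreted. The effect size is still meant to inform the next trial, so the wording is worth putting right.

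**What to change.** Delete the MCAR condition. State that missing 6-month outcomes are multiply imputed under missing at random for all randomised participants, whatever an MCAR test shows. Use one small model with arm, the baseline value of the outcome and at most one or two pre-specified recorded predictors of dropout, and not a separate many-predictor model for each arm. Derive the adjusted effect and Cohen's *d* from the imputed data. A simple sensitivity analysis that shifts imputed values by a fixed delta is optional; it would show how far departures from MAR matter.

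The cost is a change of wording, a little extra analysis and a small possible loss of precision from imputing in a small sample. No new data are needed.

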## Discussion

This trial protocol describes the pilot feasibility trial of the “Goals in Focus” intervention, a new individualized goal-focused form of CBT targeting motivational negative symptoms in people with psychosis. Feasibility and acceptability as well as first estimates of efficacy of “Goals in Focus” will be evaluated and information on possible optimization for a consecutive fully powered RCT will be gathered.

“Goals in Focus” was developed to directly target the relevant motivational negative symptom domains by translating recent empirical research on factors and mechanisms underlying motivational negative symptoms into specified interventions. The comprehensive treatment approach is tested in a randomized controlled trial design which allows to eliminate a possible selection bias and to control for spontaneous remission effects. However, there are some limitations to our study design: this is a pilot trial with the main focus on feasibility and the sample of 30 participants is not sufficient for a reliable efficacy analysis. As likelihood of type 1 error inflation is high, results of significance tests cannot be interpreted, but effect sizes derived from the present study will be used for a priori sample size calculation for a subsequent fully powered RCT. The advantage of a wait-list control condition is that it allows a first estimation of effects and enables wait-list participants to later receive the same intervention. Also, diffusion effects between the conditions (e.g., patients from the wait-list group receiving information about the intervention from other patients, therapists including intervention elements in standard treatment) are unlikely due to the outpatient setting and the fact that treatment as usual is not provided by trial therapists. A disadvantage is that the wait-list comparator may artificially inflate estimates of the intervention effect, due to participants being held in a waiting position and less likely to initiate behavioral change on their own (e.g., as suggested by Cunningham et al. [94]). Additionally, the eligibility criterium of “being able to engage in weekly therapy sessions of 50 min” limits the generalization of effects to those who are not able to attend weekly sessions for the full-time range of 50 min. Other issues that warrant mention relate to the selected outcomes: since “Goals in Focus” aims at improving goal setting and achievement, the EMA of goal pursuit is of particular interest. However, participants’ adherence to an autonomously conducted 1-week survey might be reduced, which is why we did not select it as the primary outcome. Also, a long-term follow-up was not included at this point due to the primary focus being on acceptability, feasibility, and first estimates of efficacy. It also needs to be kept in mind, that the intervention only targets motivational negative symptoms and not expressive negative symptoms, the other relevant component of negative symptoms [72, 95]. However, we expect expressive negative symptoms to be indirectly affected by the intervention as suggested by results reported by Choi et al. [18] in relation to a similar treatment approach. Accordingly, expressive negative symptoms are evaluated as a secondary outcome. Similarly, the intervention does not target contextual factors, such as social deprivation or health-related issues that are likely to exacerbate negative symptoms, but expect the achievement of personal goals due to the intervention to partially improve participants’ challenging contextual factors as well.

If found to be safe, feasible, and acceptable, the “Goals in Focus” intervention will be evaluated in a larger multicenter RCT with pre-post-follow-up design. Thus, this pilot feasibility trial will provide essential information that can be used to optimize the treatment manual, the consecutive design, and the implementation of the fully powered, multi-centered RCT. The further development and evaluation of this intervention can contribute to the much-needed extension of treatment options to support people experiencing motivational negative symptoms in pursuing their goals.

## Trial status

Patient recruitment commenced in 2020 and is scheduled to terminate in 2023 (study protocol—V.1.3, dated November 2021. With protocol submission, 14 participants had been included in the trial. Currently, 22 participants have been included in the trial (*n* = 10 were randomized to “Goals in Focus” and *n* = 12 to the wait-list control group). Dissemination of study results is planned for 2024.

## Dissemination plans

Trial results, including feasibility outcomes, will be disseminated in detail in open-access peer-reviewed scientific publications as well as summarized in consumer-friendly language on the website of Universität Hamburg. Findings will be disseminated to participants and presented at patient events and at local, national, and international conferences.

## Data Availability

Availability of data not applicable. Material can be obtained upon request from the corresponding author.
